## Abstract

**Background:**

Hypertension, affecting over 1.3 billion people globally, poses a significant public health challenge. Despite its widespread impact, hypertension management in primary healthcare settings faces challenges such as fragmented data collection, low patient adherence, and insufficient real-time monitoring. This study evaluates the effectiveness, cost-effectiveness, and implementation process of an Internet of Things (IoT)-based hypertension surveillance system designed to address these gaps in community health settings.

**Methods:**

This pragmatic quasi-experimental trial involves 2,000 hypertensive patients managed under family doctor contract services in Beijing, China. The intervention group (*n* = 1,000) utilizes an IoT-based hypertension monitoring platform, which integrates smart blood pressure devices and real-time data transmission for dynamic tracking and management. The control group (*n* = 1,000) receives standard care without IoT integration. The primary outcome is blood pressure control rate, while secondary outcomes encompass standardized management rate, measurement completion rate, referral rates and biomarker profiles. Cost-effectiveness is evaluated using administrative data on healthcare utilization and intervention costs. Qualitative data, collected through patient surveys and focus groups with healthcare providers, explores implementation barriers and user experiences.

**Discussion:**

The study aims to provide comprehensive evidence on the clinical effectiveness, cost-effectiveness, and implementation process of IoT-based hypertension management in primary care. By combining quantitative and qualitative methods, it seeks to understand how the intervention works in real-world settings and identify facilitators and barriers to its implementation. The findings could inform policy decisions and optimize resource allocation for chronic disease management in primary care.

**Trial registration:**

ChiCTR, ChiCTR2500103556.Registered 30 May 2025.

**Supplementary Information:**

The online version contains supplementary material available at 10.1186/s12913-025-13562-3.

## Background

With the accelerating global aging process, the prevalence of chronic diseases, particularly hypertension, which is a leading cause of cardiovascular diseases and stroke, has been steadily increasing, posing significant challenges to public health worldwide, affecting over 1.3 billion people worldwide [1]. According to the China Cardiovascular Disease Report 2018, 27.9% of Chinese residents aged 18 and above have hypertension. The prevalence rate of hypertension increases significantly with age. Specifically, more than 50% of those aged 65 and above are hypertensive [2]. In China, the treatment rate of hypertension among residents aged 18 and above is 45.8%, and the control rate is 16.8%. The overall prevention and treatment situation of hypertension still requires further improvement [3]. In 2013, the total health expenditure in China amounted to $462.74 billion, among which the direct economic burden of hypertension accounted for 6.6% [2]. It is estimated that the standardized community management of hypertension can save approximately $30.45 in annual per capita direct medical expenses for patients with hypertension. Moreover, an annual per capita investment of $116 in the community health management of hypertension in China can generate a positive net benefit, that is, the output exceeds the input [4]. Effective management of hypertension is not only critical for individual health but also has profound implications for the allocation and utilization of healthcare resources.

Despite widespread attention to hypertension prevention and control globally, the management outcomes remain suboptimal [5, 6]. Particularly in primary healthcare settings, hypertension management faces numerous challenges. the quality of hypertension management in primary healthcare institutions varies significantly, with notable disparities between urban and rural areas. Urban regions, with relatively abundant medical resources, tend to have more standardized hypertension management practices, whereas rural areas, due to limited healthcare resources, often struggle with inadequate management. Meanwhile, general practitioners in primary healthcare settings often lack specialized training and guidance in hypertension management, resulting in insufficient standardization and scientific rigor in their practices. In addition, some patients have an insufficient understanding of the hazards of hypertension. In rural areas, patients are often reluctant to take prescribed medications if they perceive no symptoms. Moreover, there is a shortage of general practitioners, and patients have a weak awareness of self-management, which can easily lead to the interruption of follow-ups [7]. All in all. community health centers play a critical role in hypertension management, but traditional approaches often face challenges such as fragmented data collection, lack of real-time monitoring, and low patient adherence. The integration of Internet of Things (IoT) technology into hypertension management offers a promising solution [8].

With the rapid development of the IoT technology, its application in healthcare has become increasingly feasible. IoT technology enables real-time monitoring of patients’ physiological data through sensors and smart devices, transmitting this data to cloud platforms for analysis and processing, thereby providing timely health management recommendations to both physicians and patients [9]. In Japan, the Internet of Things (IoT) is applied through the CureApp HT digital therapeutics app. A home blood pressure monitor, as an IoT device, is used by patients to measure their blood pressure daily. A total of 390 patients with essential hypertension aged 65 years or younger who were not taking antihypertensive medications were divided into two groups. The group using CureApp HT in addition to lifestyle modification guidance showed a significantly greater reduction in blood pressure compared to the control group. Moreover, in terms of cost-effectiveness, the incremental cost-effectiveness ratio of using the app under a specific model is lower than the threshold in Japan, suggesting it may be cost-effective over a lifetime [10]. In Italy, the Tholomeus^®^ web is widely used. which runs in the context of the Internet-of-Medical-Things (IoMT), with operations spanning various healthcare and home settings. It serves as a crucial telehealth platform for chronic disease management, especially hypertension. For instance, in general practices, the telehealth solution has helped family doctors better manage hypertensive patients. In hospitals, it has enabled the identification of different hypertension types and provided insights into patients’ vascular health. The home monitoring has also increased patients’ awareness of their health status, facilitating timely medical advice and potentially improving long-term health outcomes [11].

IoT-based hypertension management information systems are currently lacking in China, despite the technology’s encouraging potential in this area, particularly in primary healthcare settings [12]. Most existing hypertension management systems rely on traditional manual records and paper-based archives, making it difficult to ensure the timeliness and accuracy of data. Furthermore, these systems often lack effective integration with family physician contracting services, hindering dynamic monitoring and performance evaluation of hypertension management. Therefore, the development of an IoT-based hypertension management information system is essential to enhance the scientific rigor and standardization of hypertension management while providing primary healthcare institutions with effective tools for performance evaluation. Through devices such as smart blood pressure monitors and health huts, patients’ blood pressure data can be uploaded in real time to health management platforms, enabling physicians to monitor blood pressure trends and adjust treatment plans accordingly. Simultaneously, the system can provide real-time monitoring data for managers to evaluate the performance of family physician contracting services, thereby improving the quality of hypertension management in primary healthcare settings.

### Objectives

The general aim of this study is to evaluate the effectiveness, cost-effectiveness, and implementation process of an IoT-based hypertension surveillance system in primary healthcare settings in China. Specifically, the study addresses the following research questions:

Clinical Effectiveness: ①What are the effects of the IoT-based monitoring system on blood pressure control rates and standardized management rates compared to traditional care?②Does the intervention improve secondary outcomes, including referral rates for refractory hypertension and biomarker profiles (e.g., lipids, glucose)?Economic Evaluation: What are the incremental costs and cost-effectiveness of the IoT system versus standard care?Implementation Process: What are the facilitators and barriers to deploying the IoT system in routine primary care, as perceived by healthcare providers and patients?

## Methods

### Overall study design and setting

This study is a pragmatic quasi-experimental trial aimed at evaluating the effectiveness and feasibility of an IoT-based hypertension monitoring and management system in primary care settings. The overall study design is described in Fig. 1. The study compares outcomes between an intervention group (IG) using the IoT system and a control group (CG) receiving standard care. Quantitative data will assess clinical outcomes including blood pressure control rates, standardized management rates, and healthcare utilization, while qualitative methods will examine user experiences and implementation barriers through surveys and interviews with patients and healthcare providers (Fig. 2).

The study is carried out in Liyuan Health Center and its affiliated community health service stations in Tongzhou District, Beijing, P.R. China. The research area covers a large population of hypertension patients. It serves a population of approximately 250,000 people in urban and suburban regions, where the hypertension prevalence reaches as high as 33.3% [3]. The intervention is deployed across five family doctor teams in Liyuan Community Health Center and Xiaogao Community Health Station. These sites represent typical primary care institutions in Beijing’s urban expansion areas, serving mixed populations of long-term residents and recent migrants. The center utilizes Beijing’s municipal health information platform (B/S architecture) and has pre-existing health huts with basic measurement capabilities. The new IoT system integrates with these platforms through application program interfaces (APls) [13], enabling real-time data transmission from 6 intelligent monitors to electronic health records.

During the clinical practice application stage, all research subjects are randomly selected from the currently managed patients. 1000 hypertension patients who have signed contracts with the family doctor teams of 5 teams in Liyuan Health Center and Xiaogao Community Health Service Station where the system is deployed are selected as the intervention group. These patients use the IoT-based hypertension supervision platform for blood pressure measurement, and their data is included in the new system for statistical analysis. Another 1000 hypertension patients who have signed contracts with the family doctor teams of other subordinate stations in Liyuan Health Center where the system is not deployed are selected as the control group. They only measure blood pressure in the health huts, and their data is not included in the new system for statistical analysis.

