### Study intervention

The study intervention focuses on the development and application of IoT-based hypertension monitoring and management information system. This system integrates intelligent blood pressure monitoring devices and software to dynamically track and manage hypertensive patients in primary care settings. The intervention involves deploying six blood pressure health management all-in-one machines, two electronic display screens, and an intelligent hypertension monitoring information system in the general practice clinics of Liyuan Community Health Center and Xiaogao Community Health Station. These devices are connected to the health hut and the residents’ personal health records, enabling real-time data transmission and analysis. The system utilizes identity information, health insurance cards, and facial recognition to ensure accurate data collection and upload. The primary goal is to monitor blood pressure data, control rates, and standardized management rates. By leveraging IoT and AI technologies, the intervention seeks to enhance the efficiency and quality of hypertension management in primary care (Fig. 3).

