The system’s innovative features include interoperability with existing health hut, automated risk assessments, and intelligent decision support. It employs a modular design for scalability, enabling future expansion to additional metrics like blood glucose and weight, while standardized data formats and open interfaces facilitate integration with external platforms such as the Beijing Community Health’s electronic health record (EHR) and Tongzhou District Performance Evaluation Platform. Security is ensured through role-based access control [14]. Key functionalities include real-time data transmission (via ID card, medical insurance card, or facial recognition), dynamic tracking of standardized management and control rates, and dashboard visualization of blood pressure trends for clinicians and patients. During development, rigorous testing was conducted: 500 simulated patient datasets were used to validate system functionality, including seamless data upload to individual health records and public health systems, accurate calculation and display of monthly/quarterly metrics on clinic screens, automated risk alerts for uncontrolled hypertension, and generation of quarterly/annual trend reports. The system successfully passed testing, confirming capabilities in risk alerts, statistical analysis, and user interface usability, and is now operational in the clinical application phase. In the clinical phase, 2000 hypertensive patients are chosen at random from the current management pool to participate in the trial. The intervention group (*n* = 1,000) consists of patients from five family doctor teams in Liyuan Community Health Center and Xiaogao Station equipped with the new system, while the control group (*n* = 1,000) comprises patients from other stations without the system. The intervention group uses the IoT-based system for blood pressure measurements, with data automatically uploaded to health records and displayed on screens.

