### Participants, selection criteria and recruitment

The study targets hypertensive patients managed under the family doctor contract service at Liyuan Community Health Center and its subordinate Community Health Station in Tongzhou District, Beijing. The intervention group (IG) will consist of 1,000 hypertensive patients randomly selected from five family doctor teams at Liyuan Community Health Center and subordinate Xiaogao Station where the IoT-based hypertension monitoring system is deployed. The control group (CG) will include another 1,000 hypertensive patients from other stations without the system, matched for baseline characteristics.

Participants must meet the following inclusion criteria to be enrolled in the study. First, they must be aged 35 years or older and have a confirmed diagnosis of primary hypertension as defined by the Chinese Hypertension Clinical Practice Guidelines [17], which requires systolic blood pressure ≥ 140 mmHg and/or diastolic blood pressure ≥ 90 mmHg measured on at least two separate occasions to ensure diagnostic accuracy. Second, they must be residents within the administrative jurisdiction of Liyuan Health Center and have signed a family doctor contract, which is a prerequisite for accessing hypertension management services under the National Basic Public Health Service Program [18]. This ensures that participants are eligible for the standardized care and monitoring provided by the health center’s healthcare teams. Third, participants must demonstrate the functional capacity to attend outpatient visits either independently or with minimal assistance, excluding those who are bedridden or require full-time care. This criterion is essential to ensure that participants can engage in regular blood pressure measurements, follow-up consultations, and health assessments as required by the study protocol, thereby facilitating the collection of reliable data on hypertension management outcomes.

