Participants will be excluded if they meet any of the following criteria to ensure the safety and validity of the research results. First, individuals with a history of acute cardiovascular or cerebrovascular events, such as stroke, myocardial infarction, or aortic disease, occurring within the past 12 months are excluded, as these conditions may confound the assessment of hypertension management outcomes and require specialized clinical interventions that could interfere with the study’s standardized procedures. Second, participants with severe comorbidities, including heart failure, severe renal failure, or cancer, are ineligible, as their complex medical conditions may reduce their capacity to adhere to the study’s monitoring protocols and could lead to substantial variability in health-related outcomes. Third, individuals with uncontrolled psychiatric conditions (such as schizophrenia or severe depression with suicidal ideation) will be excluded, as these conditions may compromise study participation, data accuracy, or patient safety. Fourth, patients aged over 80 years or those with severe mobility impairment (defined as the inability to ambulate even with assistive devices) are excluded, as their limited physical capacity may hinder regular attendance and adherence to the study’s follow-up schedule. Finally, pregnant or lactating females are excluded due to the unique physiological changes and medication considerations during this period, which require specialized care outside the scope of the study’s focus on primary hypertension management in the general adult population. These exclusion criteria are designed to minimize confounding variables and ensure that the results reflect the true impact of the intelligent monitoring system on hypertension patients under routine primary care settings.

Eligible participants will be identified through Liyuan Health Center’s electronic health record (EHR) system, which maintains a registry of approximately 20,000 registered hypertension patients. The research team will use EHR data to pre-screen candidates, filtering for age, diagnosis, contract status, and exclusion criteria, after which random selection will be performed using a computer-generated random number table, stratified by age and sex to ensure demographic balance. Meanwhile, the control group (CG) will match to the intervention group (IG) on age, sex, and hypertension duration using EHR data to minimize baseline confounding.

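### Main-centre patients are only in the intervention arm and all controls come from subordinate stations, so facility type coincides with the system for main-centre patients and the stated analysis does not separate the two

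*Protocol article*

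**What the plan says.** The article describes the sites of each arm in several places, and the descriptions agree.

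- **Intervention arm.** Under Overall study design and setting: "The intervention is deployed across five family doctor teams in Liyuan Community Health Center and Xiaogao Community Health Station". The same section selects the 1,000 intervention patients from the "family doctor teams of 5 teams in Liyuan Health Center and Xiaogao Community Health Service Station where the system is deployed". Study intervention puts the devices in the "general practice clinics of Liyuan Community Health Center and Xiaogao Community Health Station".
- **Control arm.** Overall study design and setting takes the controls from the "family doctor teams of other subordinate stations in Liyuan Health Center where the system is not deployed are selected as the control group". Study intervention says that this arm "comprises patients from other stations without the system". Participants, selection criteria and recruitment repeats it: "The control group (CG) will include another 1,000 hypertensive patients from other stations without the system, matched for baseline characteristics".
- **Matching.** The control group "will match to the intervention group (IG) on age, sex, and hypertension duration using EHR data to minimize baseline confounding" (Participants, selection criteria and recruitment).
- **Analysis.** Statistical analysis compares the groups by t-test, Mann-Whitney test or chi-square test. Its subgroups are age, hypertension severity and comorbidity.
- **Limitations.** The Discussion concedes that deployment at chosen locations may cause selection bias and that unmeasured variables, with socioeconomic status as the example, could matter. It also lists the baseline matching as a strength.

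**The concern.** Xiaogao is a station, so its patients have controls at the same kind of facility. Main-centre patients have none. In the pooled comparison, part of the contrast is therefore health centre against station as well as system against no system.

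The matching variables all describe the patient. Two patients of the same age, sex and hypertension duration can still be looked after in different kinds of facility. An unadjusted chi-square test on the control rate leaves that difference in the estimate.

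Several secondary outcomes (standardized management, completion of measurements, referral, biochemical results) reflect how care is organised, so they too could differ between a centre and a station without any IoT system. With 1,000 patients per arm, even a modest difference of this kind could be statistically significant and be reported as an effect of the system.

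**Working it through.** The plan gives no figure on this point, so there is none to reproduce. The check has three parts.

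**1. Who is in which arm**

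| Facility type | With system | Without system |
|---|---|---|
| Main health centre | yes | none |
| Station | Xiaogao only | other stations |

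One of the four cells is empty. Write the system effect as *s* and the centre-minus-station difference as *f*, and assume that they add:

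- main centre v other stations = *s* + *f*
- Xiaogao v other stations = *s*
- main centre v Xiaogao, both treated = *f*
- pooled contrast = *s* + *w* × *f*, where *w* is the main-centre share of the intervention arm

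The bias of the pooled contrast is *w* × *f*. Under additivity *s* and *f* can be separated, but the separation rests on Xiaogao alone. A system effect specific to the main centre cannot be separated from *f*.

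**2. Size of the bias**

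From the plan (Sample size calculation): control rate 45%, hypothesised rate 55%, 1,000 per arm, 15% attrition, hence 850 evaluable per arm, two-sided 5% level. Assumed, because the article gives neither: *w* = 40% to 80% and *f* = 3, 5 or 10 points.

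The probability of a significant result when *s* = 0 uses the two-proportion normal approximation with patients taken as independent. Example for *w* = 0.8 and *f* = 5 points, which is a bias of 4 points (49% v 45%):

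- SE under the null = √(0.47 × 0.53 × 2/850) = 0.0242
- SE under the alternative = √((0.49 × 0.51 + 0.45 × 0.55)/850) = 0.0242
- Φ((0.04 − 1.96 × 0.0242)/0.0242) = about 0.38

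| Gap *f* | Bias at *w* = 40% to 80% | Significant with no true effect |
|---|---|---|
| 3 points | 1.2 to 2.4 points | 8% to 17% |
| 5 points | 2 to 4 points | 13% to 38% |
| 10 points | 4 to 8 points | 38% to 91% |

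**3. Precision of the station-only contrast**

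A main-centre share of 80%, 60% or 40% leaves 200, 400 or 600 patients at Xiaogao. After 15% attrition, 170, 340 or 510 are evaluable, against 850 controls. The 95% half-width is 1.96 × √(0.55 × 0.45/n + 0.45 × 0.55/850).

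| Evaluable at Xiaogao | Half-width | Power, 45% v 55% |
|---|---|---|
| 170 | 8.2 points | 67% |
| 340 | 6.3 points | 88% |
| 510 | 5.5 points | 95% |

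The pooled comparison at 850 per arm has 98.5% power. None of these figures allows for clustering by team or site.

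**The case against.** Five arguments can be made on the other side.

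- **Facility type is not beyond adjustment.** A reader might infer from the empty cell that no matching or adjustment could ever remove it. The article does not support that. Xiaogao is a treated station, so a facility-type term can be estimated if effects are additive. This stands, with the limit that the information comes from one station.
- **Baseline values help.** Study conduct has blood pressure measured at baseline in all participants. A baseline-adjusted or difference-in-differences comparison would deal with a stable level gap. This stands too, but it would not remove trends that differ during the year, and the between-group test stated for the control rate does not use baseline.
- **No facility difference is documented.** The article nowhere says that centre and stations differ in staffing, equipment or access to laboratories. It calls the intervention sites typical, the stations are subordinate to the same centre, the candidates come from one EHR registry, and controls are managed under the national specification. This stands: a difference is possible, but its existence, direction and size are unknown. The 10-point row assumes a gap as large as the whole hypothesised effect.
- **The Discussion already concedes site-related bias.** It does so in general terms, without naming centre against station and without an analysis for it. This softens the point but does not answer it.
- **Analyses by site may be in an analysis plan that is not shown.** That is possible, so their absence from the article is not held against it. The composition of the arms, the matching variables and the tests are stated in the article, and the point rests on those.

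**Conclusion.** The point holds in a limited form. As stated, the design leaves facility type and the system coinciding for main-centre patients, and neither the stated matching nor the stated unadjusted tests address it. Under the assumed shares and gaps the bias runs from 1.2 to 8 points, and with no true effect a significant result would occur in about 8% to 91% of trials. These figures illustrate sensitivity. They are not an estimate of the bias, which could be nil or act in either direction.

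It does not follow that the trial cannot inform on the system, or that a centre-station difference exists. The Xiaogao contrast is informative, but it compares one station, with its own teams and patients, with the others, so it can support a conclusion and not settle it. The remedy is a cheap improvement to the analysis and the reporting.

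**What to change.** Pre-specify a sensitivity analysis for the primary outcome that reports two contrasts separately, each with an estimate and a 95% confidence interval: main centre v other stations, and Xiaogao v other stations. Use the baseline blood pressure already collected, by baseline adjustment or difference-in-differences, and say that this removes a stable level gap but not differing trends.

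State in advance how the conclusions will be limited: if the effect is seen only or mainly in the main centre, facility type cannot be excluded as an explanation, and the Xiaogao contrast rests on a single station. A rule that credits the system whenever the Xiaogao contrast points the same way as the pooled result would be too weak, since with no true effect it would be met about half the time or more by chance. Name centre against station among the limitations.

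The cost is analysis and reporting text, with no new data and no change to recruitment. The downside is lower precision in the Xiaogao contrast: a half-width of about 8.2 to 5.5 points and power of about 67% to 95% over the assumed range of site splits, before clustering.
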